#### Menopause Status

Hormone assessments will be performed from fasting serum samples taken between 8:00 and 10:00 AM. Serum will be separated by centrifugation for 10 min at 2,200 × g. Systemic FSH levels will be immunoassayed using IMMULITE 2000 XPi (Siemens Healthcare Diagnostics, UK). Participants' menopause status will be determined based on the self-reported menstrual cycle.

Applying the categorization of (75) subjects will be categorized as postmenopausal if there has been no menstrual bleeding during the 6 previous months and following cut values will be applied FSH > 30 IU/L. Participants will write a self-report concerning their health problems, gynecologic status, and use of medications.

### Interventions

Both groups will train with a frequency of 2 weekly sessions. They will have 48 h of rest between sessions. To ensure the blinding of participants, the EX + WB-EMS group will train on Mondays and Thursdays while the EX group will train on Tuesdays and Fridays. Both groups will perform the same program consisting of endurance tasks and resistance strength exercises, but the EX + WB-EMS group will also implement a superimposed WB-EMS during the training. The training protocols will be supervised by two instructors graduated in Physical Activity And Sports Sciences with wide experience in WB-EMS training. Participants were asked not to make physical efforts outside the training program.

#### EX Group Intervention

The sessions will last 40 min. Participants will perform a 10-min warm-up by walking on a treadmill. Participants will be instructed to walk at the speed they normally would during a stroll in the park. Subsequently, participants will execute the resistance training protocol, which will consist of performing three multi-articular exercises involving push and pull actions (squat, deadlift, and bench press) as it is recommended (76–78).

The strength training will last 10 min divided into two blocks of 5 min. One block will consist of 10 sets of each exercise. Sets will be composed of two repetitions with 2 s of eccentric and 1 second of concentric phase (6 s in total per set). Between repetitions, the participants will have 4 s of rest.

The intensity of the resistance training will be 40% of the 1RM (77), assessed by an indirect measurement test (79). Following the line of (80) the absolute load will be increased by 5% every 2 weeks to apply the progressive overload principle. After the strength exercises, participants will perform 10 min of cardiovascular work on the treadmill, at a constant individualized speed, obtained from the talk test (81). The highest speed they can walk while talking will be estimated. The intensity of cardiovascular training will be increased by 5% every week. Finally, the participants will perform a 10 min stretching of the whole body's muscles as a cooldown.

At the end of each session, a scale will be presented (82) with a range from level 6 (No exertion at all) to 20 (Maximal exertion) in which the participants will record their extent of perceived exertion. The assessment will always end at 15 (Hard).

#### WB-EMS Group Intervention

The EX + WB-EMS group will perform the same training as EX group but with superimposed WB-EMS. A rectangular, bipolar compensated current of 6 s duration and 4 s of rest will be applied with a Wiemspro® electrostimulator (Malaga, Spain) (Figure 2). The weight of the complete kit does not reach 1.5 kg.

**Figure 2 F2:**
[figure not shown]
Wiemspro suit and device details.

Since there is evidence that a minimum current frequency of 50 Hz is necessary to cause adaptations in strength training (83, 84), a frequency of 55 Hz will be applied during the strength exercises, with a 60% duty cycle (pulse width: leg, glute 350 μs, lumbar, abdominal, dorsal 300 μs, Trapeze 250 μs, chest 200 μs, arm 150 μs), 800 ms of ascent ramp, and descent ramp of 500 ms. During cardiovascular training on the treadmill, the frequency will be 7 Hz with a duty cycle of 100%.

During the WB-EMS sessions, following a similar procedure used by (60), four levels will be established on a scale from 1 to 10 to control the intensity perception of the electrical current (IPC) in the participants. The levels are from 1 to 4 (mild), from 4 to 6 (moderate), from 6 to 8 (intense), and from 8 to 10 (pain). Participants will give constant information on the IPC during the session. The first 2 weeks, training will be conducted at “moderate” IPC level to promote familiarization and adaptation to the WB-EMS. The remaining 8 weeks of the intervention, the intensity will increase to an “intense” PIC level.

### Harms

Adverse events including physical injuries will be monitored by the instructors of the intervention and the responsible staff of the assessments and documented through the facility's incident reporting process.

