### Participants

The target of this recruitment is post-menopausal women between 55 and 70 years old (400 subjects) with a sedentary lifestyle at least 4 months prior to the study. They will be enrolled in the Ekke sports center in Lleida (Spain). They will be contacted by phone call to be informed about the nature of this study. All of them will be invited to attend an informational meeting where more details will be given on the benefits and possible risks that their participation in the project might entail. The subjects who show interest in their participation will be recruited, according to the exclusion criteria. They will be allocated and informed about their assigned arm by phone call by an external collaborator.

According to the shelf reporting in the IPAQ questionnaire of weekly physical activity, participants should be in a sedentary situation according to the scales provided by the Eurobarometer (74). Those who suffer from heart disease, metabolic disorders, tumor processes, or neurological disturbances will be excluded from this study. All participants will be informed of the details of the study and will sign an informed consent form before starting the investigation. The protocol of this study has been approved by the ethical committee of the Arnau of Vilanova's University Hospital, Lérida, (Spain). Participants will be informed of their voluntary participation. Taking into account the possible discomfort which WB-EMS could generate in the participants, they will be informed of their right to withdraw from the study without any prejudice or harm. The deterioration of the participant's health or any accident that could influence the correct development of the treatment will be reasons that will lead to their exclusion at any stage of the intervention. They will be also assured of their anonymity and the reporting of their views in aggregate form to protect their identities.

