### Outcomes

Assessments will be carried on during the study development as it is shown in Table 1. Participants will be asked not to take any stimulants before assessments to avoid influencing the results. The data will be recorded in a spreadsheet that will be stored in an encrypted USB by an external collaborator, to guarantee the privacy of the participants. He will assess the safety and validity of the research data. A blinded statistician will have access to the final dataset of the study.

**Table 1 T1:** Overview of the assessments schedule at baseline and follow-ups.

**Activity/Assessment**	**Study Period**				
	**Pre-study**	**Baseline**	**Intervention**	**Post-estudy**	**6 month Follow-up**

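### Harms go only into the facility's incident process with no stated active enquiry, so discomfort and muscle symptoms may be missed in both arms and could be noted unevenly between them

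*Protocol article*

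**What the plan says.** The Harms section is one sentence. It names the observers, "Adverse events including physical injuries will be monitored by the instructors of the intervention and the responsible staff of the assessments", and the record: events are "documented through the facility's incident reporting process".

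Four other places bear on it:

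- **Participants.** The plan expects that the current may be unpleasant enough to prompt withdrawal: "Taking into account the possible discomfort which WB-EMS could generate in the participants, they will be informed of their right to withdraw". Health deterioration or an accident leads to exclusion at any stage. No later harms contact is stated.
- **EX Group Intervention and WB-EMS Group Intervention.** "At the end of each session, a scale will be presented", on which women record perceived exertion from 6 to 20. This applies to both arms, because "The EX + WB-EMS group will perform the same training as EX group but with superimposed WB-EMS". In the WB-EMS arm there is also a 1 to 10 scale of perceived current intensity (IPC), whose top band, 8 to 10, is labelled pain. "Participants will give constant information on the IPC during the session".
- **Outcomes and Table 1.** Assessment data go into a study spreadsheet, and "A blinded statistician will have access to the final dataset of the study". Table 1 lists the assessments at T0, T2 and T3, with no row for harms.
- **Blood Test.** Creatine kinase is measured to analyse muscle damage from the exercise. Table 1 schedules it at T0, T2 and T3 in both arms.

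**The concern.** An incident reporting process suits accidents at a venue. It is a weak instrument for the harms this plan expects. Discomfort and muscle damage need not look like incidents, and they can show at home after a session. Such events reach the record only if a woman mentions them or a member of staff notices and judges them reportable.

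The route is weakest where information matters most. A woman who stops because of discomfort, or who is excluded after a health event, no longer attends sessions. After T2 no contact is stated until T3.

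There is also an opening for uneven recording. WB-EMS women report continuously on a scale that includes pain, in sessions supervised by instructors who are also harms observers. EX women are asked about effort, not pain.

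What is at stake is the safety message. The Discussion says that the method is widely used without specific legislative control, and it promises practitioners a feasible, validated programme. A short list of incidents, gathered passively, would be a poor basis for saying that the programme was well tolerated.

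**Working it through.** The plan gives no harms figure (no event rate, reporting rate or harms power), so there is nothing to reproduce. The check sets the text out by period and adds simple arithmetic for scale.

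**Where an event could be picked up, as written**

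| Period | Contact stated | Active harms enquiry stated | Same in both arms? |
|---|---|---|---|
| During sessions | Instructors, twice a week | None; exertion rating at the end | Exertion yes; IPC with pain band in WB-EMS only |
| Between sessions | Next session | None | Yes |
| On stopping or exclusion | None stated | None | Yes |
| T2 and T3 | Assessment staff | None; creatine kinase measured | Yes |
| Between T2 and T3 | None stated | None | Yes |

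**Contact time**

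- Inputs: 2 sessions a week for 10 weeks (Interventions; Experimental Approach), 40 min each (EX Group Intervention).
- Supervised time: 20 × 40 = 800 min = 13.3 h, out of 10 × 7 × 24 = 1,680 h. 13.3 / 1,680 = 0.8%, equal in both arms.
- Training days are Monday and Thursday, or Tuesday and Friday, so a woman still attending meets staff again within 3 to 4 days.
- Follow-up: taking 6 months as about 26 weeks (an assumption), 26 / (10 + 26) = 72% of the weeks lie after the intervention, with no contact stated until T3.

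These figures describe when staff are present. They do not measure the share of events missed.

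**What the trial could say about harms even with complete recording**

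With zero events among n women, the exact one-sided 95% upper limit on the event risk is 1 − 0.05^(1/n).

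- n = 14 per arm (planned): 1 − 0.05^(1/14) = 0.193, about 19%.
- n = 11 per arm (half of the 22 required before the dropout allowance): 1 − 0.05^(1/11) = 0.238, about 24%.

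With so little information per arm, a few events missed, or noticed in one arm only, could change the impression that a reader takes away.

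**The case against.** The strongest reply is that the harms rule is the same for both arms: same staff roles, same record, same number of sessions. IPC is described as a means of controlling current intensity, and nothing says that its ratings enter the adverse event record. Assessment staff see both arms at T2 and T3, and creatine kinase is measured in both. Excluding women for health deterioration presupposes that staff learn of it. The wording of questions, grading, reporting windows and data transfer are details that an article commonly leaves to the full protocol.

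Much of this stands, and it rules out several stronger readings that a reader might infer:

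- *Only WB-EMS women are asked about sensations in session.* Not so: both arms rate exertion every time. Only the continuous scale with a pain band is specific to WB-EMS.
- *Recording differs by arm.* The text shows only that it could, because one arm gives its supervising instructors more information about pain.
- *Nearly all events are lost because supervision covers 0.8% of the time.* Clock time is not the chance to report; a woman still attending can mention a problem at her next session.
- *A quarter of the women, 7 of 28, leave with no harms record.* The 25% is a planning allowance with no stated cause, and nothing says that those women's events go unrecorded.

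The reply does not remove the core. The article does not merely omit detail; it names a method, and that method is a venue's incident process. Meeting staff is a chance to volunteer an event, not an enquiry about one. An exertion rating is not a harms question. Creatine kinase at three time points cannot record symptoms, injuries or reasons for stopping during the 10 weeks.

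**Conclusion.** The concern holds in a limited form. As written, harms data would be passive: the only named record is the facility's incident process, with no stated active enquiry between sessions, on stopping or exclusion, or between T2 and T3. Under-recording of discomfort and muscle symptoms is likely in both arms; uneven recording between arms is possible but not shown.

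The number of events lost cannot be derived, because the document gives no event or reporting rate. The conclusion assumes that the Harms section describes the route actually used, and that a full protocol, not shown here, does not replace it. The missing harms row in Table 1 would not be a finding alone; it matters only because no stated step brings harms into the study data.

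This does not threaten the fitness outcomes. It limits what the trial can say about safety, and it is cheap to correct.

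**What to change.** 1. Keep the facility process for venue incidents, but make the study dataset the trial's harms record.
2. Ask both arms the same short scripted question about health problems since the last contact: at each session, at T2, at T3, and once when a woman stops or is excluded.
3. Enter the date, a description, the seriousness, and whether training was changed or stopped.
4. Add a harms row to Table 1 covering T1 to T3.
5. Report events and harm-related withdrawals by randomised arm. Report IPC ratings separately, because only one arm gives them.

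The cost is about a minute per session for instructors already present, one call per withdrawal, and a log sheet. More minor events will be reported in both arms. The change leaves the training and the current as they are. It does not make the harms comparison confirmatory: at 14 per arm it stays descriptive, and the report should say so.

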### Outcomes

Assessments will be carried on during the study development as it is shown in Table 1. Participants will be asked not to take any stimulants before assessments to avoid influencing the results. The data will be recorded in a spreadsheet that will be stored in an encrypted USB by an external collaborator, to guarantee the privacy of the participants. He will assess the safety and validity of the research data. A blinded statistician will have access to the final dataset of the study.

**Table 1 T1:** Overview of the assessments schedule at baseline and follow-ups.

**Activity/Assessment**	**Study Period**				
	**Pre-study**	**Baseline**	**Intervention**	**Post-estudy**	**6 month Follow-up**
			**(10 weeks)**		
**TIME POINT**	**T-1**	**T0**	**T1**	**T2**	**T3**
Eligibility	x				
Informed consent	x				
Randomization	x				
**INTERVENTIONS**					
Exercise group (EX)		x			
Exercise + WB-EMS group (EX+WB-EMS)		x			
**ASSESSMENTS**					
Physical fitness: Balance, leg flexibility, arm flexibility, leg strength, arm strength, agility, speed, cardiovascular endurance		x		x	X
Mean velocity (m·s-1) and the mean power of exertion (w)		x		x	x
Body composition: Weight (kg), height (cm), body mass index, body fat percentage, fat mass (kg), Visceral fat (kg), lean mass (kg), Abdominal fold, Contracted arm fold, waist perimeter, hip perimeter and Sum six folds (%).		x		x	X
Blood test: Creatin Kinasa, HDL cholesterol and triglycerides, Sodium and potassium, Thyroid Stimulating Hormone (TSH), Glycohemoglobin A1c (HbA1c)		x		x	X
Lifestyl & Health behavior: Physical activity questionnaire (IPAQ): Vigorous physical activity (AFV), Moderate physical activity (AFM) or Walking		x		x	x

#### Physical Fitness

One of the evaluations of the physical performance will be carried out by the EXERNET test consisting of 8 tests modified and previously adapted from the “Senior Fitness Test Battery” and “Eurofit Testing Battery” (85).

1. Balance: “Flamingo test.” Participants will start standing, with both feet on the ground. After the signal, they will try to stand on the sole of one foot. The time the subject can stay in that posture up to a maximum of 60 s will be recorded. The test will be performed alternately, twice with each leg. The best attempt of the four will be registered.

2. Leg strength: “Chair Stand Test.” The participant will start from a sitting position with her arms crossed and the palms of her hands resting on her shoulders. The number of times she will be able to get up and sit in 30 s will be registered. The test will be performed only once.

3. Arm strength: “Arm Curl Test.” Participants will sit on a bench holding a 2.5-kg dumbbell. The maximum number of elbow's flexo-extension that the participant will be able to execute in 30 s will be registered. The test will be performed once with each arm.

4. Legs flexibility: “Chair Sit-and-Reach Test.” Participants will begin the test sitting, with one leg extended and the heel resting on the floor, while her hands will be directed toward the toes of that leg. The existing distance, positive or negative, in centimeters, between the fingers and toes will be registered. The test will be performed once with each leg.

5. Arms Flexibility: “Back Scratch Test.” The participant will place a hand over the shoulder of that same arm, and the opposite hand from the bottom up, trying to touch each other. The participant will try to touch or overlap the fingers of both hands. The distance in centimeters (positive or negative) between the fingertips of each hand will be registered. The test will be carried out twice, once with each arm.

6. Agility: “8-Foot Up-and-Go Test.” From a sitting position, the seconds that the participant will take to get up, walk to a cone located at 2.45 m, go around it, and sit down again will be registered. The test will be performed twice with at least 1-min rest between repetitions and the best result will be recorded.

7. Speed: “Brisk Walking Test.” The time taken for each participant to walk 30 m will be measured. Two repetitions will be performed with a minute of rest between them. The best of both results will be recorded.

8. Cardiovascular resistance: “6-Min Walk Test.” In a circuit of 46 meters delimited by cones, the distance in meters that each participant will be able to cover walking for 6 min will be registered.

In addition to the mentioned evaluations, a progressive resistance test (PRT) (86) will be carried out to make a more accurate assessment of the strength development. The PRT permits simultaneous direct calculations of strength (N), velocity (m·s-1). and power (w), produced with different loads, and at the same time. Taking into account that as a consequence of aging, losses in strength are observed mostly in the type II fibers (87), the mean velocity and the mean power of exertion will be assessed in this study.

Following the PRT test protocol, we will assess the mentioned variables with the execution of 6 to 8 series of 2 to 3 repetitions in squat and bench press, applying the maximum acceleration possible, alternated with rest intervals of 2–5 min. The rest period is proportional to the intensity and duration of the effort, to avoid the prediction errors caused by the accumulated fatigue. The load will be increased progressively with the series. For each magnitude of weight lifted, it is necessary to select the repetition with which the highest values of average velocity and power are reached, as this factor expresses the highest mechanical efficiency of the exercise (88). In this study, the best repetition of the best series will be recorded. Then, the load in which that best series is done in the pre-test will be used in the post-test to compare the evolution of the variables after the intervention in the post-test 1 and the follow-up.

To perform this test a lineal encoder Chronojump® (Bosco–System, Barcelona, Spain) will be used in order to detect the position of the resistance during linear movements. This data permits an estimate of the range of movement, acceleration, velocity, strength and the power produced during each action (89).

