### Statistical Procedures

After checking normality and homogeneity assumptions, the effectiveness of different training programs on quantitative dependent variables will be assessed by a 2 × 2 mixed ANOVA. Group training intervention (“EX+WB-EMS,” “EX”) will be included as between-subjects factor, improvement (“10 weeks from Baseline,” “6 months from Baseline”) will be included as the repeated within-subjects factor, and group ^*^ improvement will be included to account for the interaction effects. Whenever a significant main effect or interaction will be observed, Bonferroni's *post hoc* correction will be used to aid interpretation of these main effects or interactions, either between-subjects factor at whatever time point or within-subjects factor at whatever group (102, 103). Hedge's *g* effect size (*g*) will be calculated and interpreted as follows *g* < 0.20 = trivial, *gfrom*0.20*to*0.50 = *mild, g* from 0.50 to 0.80 = moderate and *g* > 0.80 = large (104). Whenever the data fails to meet assumptions, robust methods will be performed following procedures of (105) and the explanatory measure of effect size (ξ) will be calculated and interpreted as suggested by (106). Values of ξ = 0.10, 0.30, and 0.50 correspond to small, medium, and large effect sizes, respectively. The qualitative ordinal variables will be analyzed with a 2 × 2 rank-based ANOVA following directions from (107). Significance level will be set at α= 0.05. The statistician will be blinded to both groups during data analyses. Intention-to-treat analysis will be performed for the primary and secondary outcomes. If necessary, a multiple imputation technique will be used to handle missing data. All analyses will be performed with JASP (version 0.11.1; JASP Team (2019), University of Amsterdam, the Netherlands) and with statistical software R Core Team (2019) for Mac and WRS2 package (108).

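### The progressive resistance test is scored as a best-of-all-loads value at baseline but at one result-selected load afterwards, which on average understates each arm's change in power and may shrink, but cannot create, a difference between arms

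*Protocol article*

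**What the plan says.** The Physical Fitness section of the protocol article adds a progressive resistance test to the EXERNET battery "to make a more accurate assessment of the strength development". Two outcomes are taken from it: "the mean velocity and the mean power of exertion will be assessed in this study". The test involves "the execution of 6 to 8 series of 2 to 3 repetitions in squat and bench press", and "The load will be increased progressively with the series".

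Two scoring rules follow. First, "In this study, the best repetition of the best series will be recorded". Second, "the load in which that best series is done in the pre-test will be used in the post-test to compare the evolution of the variables", and this applies at both the 10-week test and the 6-month follow-up.

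The section does not say which of the two outcomes decides what counts as best. Nor does it say whether the full run of loads is repeated at the later visits. It says only that the comparison is made at the load chosen at baseline.

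Under Statistical Procedures the analysed quantity is improvement from baseline, at 10 weeks and at 6 months, by group. The baseline value therefore enters every change score.

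**The concern.** The two ends of the change score are measured by different rules.

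- **Selection.** The baseline figure is the highest of 12 (6 × 2) to 24 (8 × 3) attempts, and its load is chosen because it gave that figure. Part of what makes it the highest is chance. Later figures come from 2–3 attempts at that load, with no such selection, so the average change is pulled down.
- **Load shift.** Power peaks at an intermediate load. If maximal force rises, the peak moves to a heavier load, and a comparison held at the old load misses part of the rise in peak power.
- **Undefined best.** Velocity falls as load rises, so the fastest series will usually be the lightest, while the most powerful lies in the middle. One undefined best series can lead assessors to fix different loads.

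At stake are the size of each arm's reported power improvement and, under conditions set out below, some of the contrast between arms. The article plans for 28 women and claims sensitivity only down to d = 0.60.

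**Working it through.** The plan states no figure for this test, so there is nothing to reproduce. The document inputs are 6–8 loads, 2–3 repetitions, and the two scoring rules. **Noise, load range and curve shape are not in the documents and are assumed**; two different models are used to show the range.

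**1. Selection and load shift together (parabolic curve).** Seven loads x from 30% to 90% of 1RM and three repetitions. Relative power is 1 − 3.2(x − 0.55)². A strength gain g changes it to (1 + g)[1 − 3.2(x/(1 + g) − 0.55)²]. Noise is 3% or 6% per series and the same per repetition, with 100,000 simulated women. Baseline is the maximum over all loads; the later value is the best of three repetitions at the load that won at baseline.

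| True change in peak power | Recorded, 3% noise | Recorded, 6% noise | Best of all loads at both visits |
|---|---|---|---|
| 0% | −2.4% | about −6% | about 0% |
| 5% | +2.3% | −1.4% | about 5% |
| 15% | +10.6% | +6.8% | +15.5% to +16.1% |

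**2. Splitting the 15% case.** Without noise, power at the old 55% load after a 15% gain is 1.15 × [1 − 3.2(0.55/1.15 − 0.55)²] = 1.131, or +13.1%. Load shift therefore costs 15 − 13.1 = 1.9 points. Selection costs the rest: 13.1 − 10.6 = 2.5 points at 3% noise and 13.1 − 6.8 = 6.3 points at 6%.

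**3. A second model (linear load–velocity line).** Loads from 20% to 80% of maximum, repetition SD 3%. With no true change, and over 6–8 loads, the recorded mean change is about −2% to −3% (series SD 3%), −4% to −5% (SD 5%) and −9% to −11% (SD 10%). With zero noise it is zero.

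**4. Load shift alone, noise-free, second model.** Power at load x is proportional to x(1 − x/F), with F the maximal force. The best baseline load is x = 0.5. If F rises by g, peak power rises by g, but power at the old load rises only by 1 − 1/(1 + g):

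- g = 10%: 1 − 1/1.1 = 9.1%
- g = 20%: 1 − 1/1.2 = 16.7%
- g = 30%: 1 − 1/1.3 = 23.1%

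If the gain is in velocity only, the best load does not move and nothing is missed.

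**5. Between arms.**

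- Equal true gains: bias 0.0 points.
- Force gains of 20% against 10%: the true 10 points appears as 7.5–7.6 (first model) or 7.7–7.9 (second model). The noise-free check is 16.7 − 9.1 = 7.6.
- Velocity gains of 20% against 10%: 9.7–9.9 points.

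**6. Spread.** From measurement error alone, in the first model with a true 10% gain, the SD of the recorded change is about 5.4 points, against 4.5 when all loads are scored at both visits (3% noise), and about 9.7 against 8.3 (6% noise).

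**7. Velocity at a fixed load.** On the linear line, a force gain g raises velocity at load x by (1 − x/(1 + g))/(1 − x) − 1. For g = 10% this is +2.3% at a 20% load, +9.1% at 50% and +36% at 80%. A fixed load does register a strength gain, but least of all at the lightest load, which is the one chosen if fastest means best.

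**The case against.** The strongest reply is that selection reaches no planned test. The 2 × 2 ANOVA crosses group with two improvements that share one baseline. An inflated baseline drops out when those improvements are compared with each other, and it is the same on average in two randomised arms scored alike. The stated aim is the isolated effect of WB-EMS, which is a between-arm question. **This stands.** What selection distorts is the size of each arm's own power improvement. It would distort a within-arm test only if baseline were itself a level of the repeated factor, as in the sample-size paragraph.

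Four stronger readings are tempting, and the documents do not support them:

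- *Every power gain is understated.* The bias is in the mean. In the simulations about 10–30% of women still show a recorded gain above their true one.
- *The rule biases the test of WB-EMS.* It can shrink a real difference, and only materially if force gains differ by arm. It produces no difference where there is none.
- *Fixed-load velocity is invalid.* Comparing velocity at one absolute load is legitimate. If the fastest series is nearly always the lightest, noise hardly affects the choice of load, and selection bias in velocity is then small.
- *The full series is dropped after baseline.* The text fixes where the comparison is made; it does not say what else is performed.

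It is also fair to say that chair stand and arm curl measure leg and arm strength separately and are untouched by this rule.

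**Conclusion.** The point holds in limited form. The scoring asymmetry is in the text. Followed as written, it understates the average within-arm change in mean power: by about 2–6% when nothing has changed, for assumed noise of 3–6%, more if noise is larger, and nothing if there is none. That part cancels between arms.

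The contrast between arms loses about a quarter of a real difference (10 points shown as 7.5–8) only where gains come from force and differ by arm. With pure velocity gains the loss is negligible. Change scores are noisier than they need be. The error is toward missing an effect on power.

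Separately from any simulation, the best series needs a definition for each outcome. All sizes rest on assumed noise and assumed load curves; the direction rests on the two quoted rules and some measurement noise. This should be corrected, but it does not undermine the randomised comparison.

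**What to change.** **Power.** Score it by the same rule at baseline, 10 weeks and 6 months: best mean power over all loads at each visit. In the simulations this returns about 0% for no change and close to the true gain otherwise.

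**If the fixed load is kept.** Once the load is chosen, take a separate baseline set at it and use that set, not the selected maximum, as the comparator. This removes the selection bias. It does not remove the load-shift attenuation: in the second model at 5% series noise, force gains of 20% and 10% are recorded as 17.0% and 9.3%, a difference of 7.7 instead of 10.

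**Velocity.** Define its load separately, by a rule that does not use the test result (for example, the load nearest a stated percentage of estimated baseline 1RM). Compare velocity at that same absolute load at every visit.

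**Cost.** One paragraph in the test procedure. If the full series is already run at the later visits, nothing more. If only one load was planned there, the added rest is appreciable: 6–8 series have 5–7 intervals of 2–5 minutes, so 5 × 2 = 10 to 7 × 5 = 35 minutes per exercise, and 20–70 minutes for squat and bench press together. The separate baseline set adds only a few minutes.
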